### Sample size

The hypothesis of the present trial is that 30-day all-cause mortality in patients treated with NIV will be lower than those treated with IMV. According to previous studies, the mortality rate of ARF immunocompromised patients is from 30% to 90% [1–4]. We used the data from the Fig. 4 of our previous meta-analysis to calculate the sample size, i.e. 30-day mortality in IMV-treated patients of 125/168 (75%) [21], and 85/168 (50%) [21] in NIV-treated patients, 88 patients are needed in each group to establish non-inferiority with 90% power and a 1-sided 5% type I error rate. Assuming that 25% of patients would be lost after the enrollment, thus at least of 236 patients are required.

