**Fig. 1 Fig1:**
[figure not shown]
Diagram of the study protocol according to CONSORT

The NIV group will receive NIV as the initial mechanical ventilation (MV) strategy, irrespective of whether IMV is used later during the following treatment. The IMV group will receive IMV as the initial MV strategy, irrespective of whether NIV is used later during the following treatment (Fig. 2).

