#### Implementation of interventions

##### NIV

NIV will be delivered to the patient through a mask with built-in oxygen transport tube. The mask will be adjusted and connected to a ventilation system with oxygen concentration monitor. The initial mode will be BiPAP. In all patients, the settings of NIV will be titrated by a standard protocol: the initial settings for positive end-expiratory pressure (PEEP), FiO_2_ and Inhale Positive Airway Pressure (IPAP) will be 2 cm H_2_O, 40% and 10 cm H_2_O, respectively. PEEP levels will be adjusted in increments of 2 to 3 cm H_2_O, up to a level of 10 cm H_2_O, to obtain a FiO_2_ < 70%. All settings will be adjusted every 10 min to achieve oxygen saturation ≥ 90%, a respiratory rate < 25 breaths/min, disappearance of accessory muscle activity, and arterial blood gas tests showing PaO_2_ 60–90 mmHg, PaCO_2_ 35–45 mmHg, pH 7.35–7.45. Periods of NIV will last at least 1 h and alternate every 4 h with periods of spontaneous breathing, mouth cleaning or feeding. During 30 to 40 min’ intervals, patients breathe oxygen spontaneously while pulse oxygen saturation is continuously monitored and can be maintained above 90%.

We will continuously monitor arterial oxygen saturation, heart rate and respiratory rate in all patients. Once stabilized, patients will be reassessed every 1 h to decide the duration of NIV treatment, according to clinical assessment by the primary care team without any involvement in the research team based on the following criteria.

Criteria for NIV weaning: NIV support will be reduced progressively in accordance with clinical improvement and eventually discontinued when the patient maintains a respiratory rate < 25/min and PaO_2_ > 85 mmHg with FIO_2_ < 50% and PEEP <5 cm H_2_O and relief of respiratory distress for a period of at least 12 h.

Criteria for intubation: Patients in whom NIV fails will undergo endotracheal intubation and receive IMV. The predetermined criteria for intubation are: persistent or worsening respiratory failure at any time during the NIV treatment (high parameter settings of NIV such as FiO_2_ > 70%, PEEP > 10 cm H_2_O or IPAP > 20 cm H_2_O, failure to maintain a PaO_2_/FiO_2_ ratio > 85, respiratory rate > 35/min, PaCO_2_ > 50 mmHg or a pH < 7.30, hemodynamic instability, face mask intolerance, airway bleeding, neurological deterioration, persistent vomiting and non-compliance with NIV treatment.

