##### MV

IMV will be initially performed by using the volume controlled mode, but could be adjusted to pressure controlled mode or other modes based on clinical situation such as diseases easy to develop pneumothorax, etc. The initial settings for positive end-expiratory pressure (PEEP), FiO_2_ and tidal volume (VT) will be 5 cm H_2_O, 40% and 6 ml/Kg. PEEP levels will be adjusted in increments of 2 to 3 cm H_2_O, up to a level of 20 cm H_2_O, to maintain oxygen saturation > 90%. Similar to the NIV group, the duration of IMV periods will be decided by the primary care team based on the following criteria.

Criteria and procedure for IMV weaning: IMV support will be reduced progressively in accordance with clinical improvement and discontinued if the cause for respiratory failure has been controlled, the patient maintains a respiratory rate < 25/min and PaO_2_ > 85 mmHg with FIO_2_ < 50% and PEEP <5 cm H_2_O for a period of 12 h. After a successful result of spontaneous breathing trials (including the endotracheal tubing oxygen supply, the pressure support lower than 5 cm water, or continuous positive airway pressure lower than 5 cm water for 30 min, and the Rapid Shallow Breathing Index (Tobin Index) is less than or equal to 105) has been obtained, the endotracheal tube will be extubed, and IMV support will be transferred to oxygen support via Venturi mask.

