#### Secondary endpoints

In-hospital mortality.Length of stay in hospital.Length of mechanical ventilation.Nosocomial infections (diagnosed according to the criteria of Centers for Diseases Control and Prevention [34]).Seven-day organ failure as indicated by the Sequential Organ Failure Assessment score.Adverse events of intervention (such as facial ulceration, stomach dilatation).Failure of mechanical ventilation: The transfer of NIV to IMV as well as death within 30 days in NIV group will be considered as failure of NIV; Death within 30 days in IMV group will be considered as failure of IMV.)Improvement of oxygenation: increase of oxygenation index by 100 compared to baseline or to 200 and above after 45 min of mechanical ventilation.Continuous improvement of oxygenation: Improvement of oxygenation could be maintained till weaning or transfer of mechanical ventilation. Proportion of patients intubated at 30 days (both groups). Proportion of patients intubated and weaned at 3 days (both groups). Ventilator-free days Proportion and timing of tracheostomy.

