### Statistical analysis

All data will be analyzed based on the intention-to-treat (ITT) principle. All analysis results and findings will be reported according to CONSORT statement recommendations [37]. Descriptive statistics will be used to comparing the baseline features of the groups established by randomization. All tests will use a significance level of 0.05 and be performed using SAS 9.4 (TS level 1 M2; Cary, NC, USA).

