#### Secondary endpoints

Continuous variables including length of stay in hospital, length of mechanical ventilation and seven-day organ failure will be reported as mean and standard deviation or as median and interquartile range, and compared between the two groups using Wilcoxon tests. Dichotomous variables including in-hospital mortality, nosocomial infections, adverse events of intervention, failure of mechanical ventilation and improvement of oxygenation will be reported as absolute and relative frequencies, and compared with the χ^2^ test between the two groups. Similar subgroup analysis procedures described above for primary endpoint will also be used. Kaplan-Meier estimator will be used to compare median hospital and ICU length of stay between the two groups. The event of interest and the censoring event are discharge alive and death, respectively. Intubation rate in NIV group and weaning rate in IMV group will be reported as absolute and relative frequencies. Independent variables associated with intubation rate and weaning rate will be explored with Logistic analysis model with a *p* < 0.03 in a step-by-step, backward-forward approach. In accordance with our hypothesis, the ventilatory approach and disease severity will be both forced in the model.

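### Intubation at 30 days, listed for both groups, is not a fair two-arm outcome: ever intubated is near 100% in the IMV arm by assignment, and status on day 30 counts the dead as not intubated

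*Protocol article*

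**What the plan says.** The list under Study outcomes, Secondary endpoints, includes "Proportion of patients intubated at 30 days (both groups"). It does not say whether this means ever intubated by day 30 or intubated on that day, and it gives no rule for patients who have died.

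The secondary-endpoint paragraph of Statistical analysis describes intubation by arm: "Intubation rate in NIV group and weaning rate in IMV group will be reported as absolute and relative frequencies". The same paragraph then plans a logistic model for factors associated with intubation and weaning, with ventilatory approach and disease severity forced in.

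Three other places determine what the endpoint can measure:

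- Study interventions: "The IMV group will receive IMV as the initial MV strategy, irrespective of whether NIV is used later during the following treatment".
- The NIV subsection: "Patients in whom NIV fails will undergo endotracheal intubation and receive IMV". In that arm, intubation follows failure of the assigned treatment.
- The subsection on invasive ventilation, on the end of weaning: "the endotracheal tube will be extubed, and IMV support will be transferred to oxygen support via Venturi mask". Invasive ventilation therefore means a tube in the airway.

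Statistical analysis opens with "All data will be analyzed based on the intention-to-treat (ITT) principle". Sample size gives the expected 30-day mortality: "30-day mortality in IMV-treated patients of 125/168 (75"%) and "85/168 (50%) [21] in NIV-treated patients".

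**The concern.** An outcome compared between randomised arms should be free to vary in both and should not improve because patients die. This one can fail on either count. If it means ever intubated, one arm's value is set by the allocation. If it means intubated on day 30, a death removes a patient from the numerator but not from the intention-to-treat denominator, in a trial planned around a large mortality difference.

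At stake is how this secondary result is read. A table with intubation in both columns invites the reader to see a benefit of NIV under one reading and a harm under the other, when much of either difference could come from the assignment or from mortality. The choice also reaches the planned logistic model, because the data set for that model depends on which arms have an intubation outcome.

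**Working it through.** **Inputs.** Planned 30-day mortality is 75% (IMV) and 50% (NIV), from Sample size. The 88 per arm comes from the same section and serves here only as an illustrative size. The intubation rate after NIV and the share of survivors still intubated are not in the document; they are assumptions, shown as ranges.

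**The plan's own figure.** The endpoint has no figure of its own. The 88 per arm is reproduced from the Interim analysis description (two-sided 0.05, 90% power, 0.75 v 0.50, continuity correction, three looks):

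- Pooled variance: (1.960 + 1.282)² × 2 × 0.625 × 0.375 / 0.25² = 78.8.
- Inflation of 1.0123 for the stated boundaries (by simulation): 79.8.
- Continuity correction, n/4 × [1 + √(1 + 4/(0.25n))]²: 87.6, so 88.
- Dropout: 88 / 0.75 = 117.3, so 118 per arm and 236 in total.

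**Reading A: ever intubated by day 30.** Let p₁ be the IMV proportion and p₂ the NIV proportion, with p̄ their mean. Then z = (p₁ − p₂) / √[p̄(1 − p̄) × 2/88].

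| NIV rate (assumed) | p̄ if IMV = 100% | z if IMV = 100% | z if IMV = 95% |
|---|---|---|---|
| 20% | 0.60 | 0.80 / 0.0739 = 10.8 | 10.1 |
| 40% | 0.70 | 0.60 / 0.0691 = 8.7 | not shown |
| 60% | 0.80 | 0.40 / 0.0603 = 6.6 | 5.6 |

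The difference is large across the range, even if 5% of the IMV arm is never intubated, and most of it is the allocation.

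**Reading B: intubated on day 30, all randomised patients in the denominator.** Let s be the share of survivors intubated on day 30.

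- IMV: (1 − 0.75) × s(IMV) = 0.25 s(IMV).
- NIV: (1 − 0.50) × s(NIV) = 0.50 s(NIV).
- Ratio NIV/IMV = 2 × s(NIV)/s(IMV).

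The factor of 2 is the ratio of survival. It multiplies whatever real difference exists among survivors.

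| s(IMV) (assumed) | s(NIV) (assumed) | IMV proportion | NIV proportion |
|---|---|---|---|
| 10% | 10% | 2.5% | 5% |
| 20% | 20% | 5% | 10% |
| 40% | 40% | 10% | 20% |
| 20% | 10% | 5% | 5% |
| 40% | 10% | 10% | 5% |

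With equal survivor shares, NIV shows twice the proportion because twice as many of its patients are alive. With half the survivor share in NIV, the arms look identical. The observed direction therefore depends on the true shares. For the 5% v 10% row at 88 per arm, z = 0.05 / √(0.075 × 0.925 × 2/88) = 0.05 / 0.0397 = 1.26, short of significance. If mortality were equal, the factor would be 1 and this distortion would vanish.

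**Survivors only.** Restricting the denominator to survivors does not rescue the comparison. It conditions on an outcome after randomisation that is planned to differ (25% v 50% alive).

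**The logistic model.** With the NIV arm alone, ventilatory approach is a constant and its coefficient cannot be estimated. With both arms pooled under reading A, almost every IMV patient has the event, so arm nearly separates the outcome.

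**The case against.** The strongest reply is that no between-arm test of this endpoint is stated. The dichotomous variables named for the χ² test do not include it, and intubation is to be given as frequencies. Listing it for both groups may only mean tabulating it in each arm. That has a use: it shows how many IMV patients were actually intubated and how many NIV patients crossed over. This stands in part. The χ² list is introduced as examples and is not closed, but a reader who infers that a significant result is built into the plan goes too far. The z values describe what would happen if the test were run.

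Second, the two sections need not conflict. The analysis section does not say that intubation will be reported in the NIV group only, and it also passes over other listed endpoints, such as ventilator-free days and tracheostomy. This stands: the sections are misaligned, not flatly contradictory.

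Third, a reader might infer that the day-30 reading guarantees a spurious harm of NIV whatever the true effect. The document does not support that. The pattern needs unequal mortality and similar survivor shares, and nothing in the article supports equal shares, since the arms reach intubation by different routes.

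Fourth, failure of mechanical ventilation and ventilator-free days are already listed and might serve instead. This does not rescue the endpoint. Failure is defined differently by arm (transfer or death in NIV, death alone in IMV), and the article states no rule for deaths in ventilator-free days.

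**Conclusion.** The point holds as a defect of one secondary endpoint. Under neither reading is intubation at 30 days a fair two-arm outcome, and its listing should be aligned with the analysis section.

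Under the ever-intubated reading this follows from the assignment; only the z values rest on assumed NIV rates. Under the day-30 reading, counting the dead as not intubated is an inference from the intention-to-treat statement, since the article gives no rule for deaths. The twofold factor rests on the planned mortality; its translation into 5% v 10% rests also on an assumed equal 20% of survivors intubated.

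It would be wrong to infer from this that the trial's main result is at risk. The primary endpoint and sample size are untouched. The change is worth making because a two-arm table of this endpoint would be easy to misread and because the intubation model cannot be fitted sensibly with arm forced in.

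**What to change.** 1. In the list of secondary endpoints, restrict intubation by day 30 to the NIV arm, as a descriptive cumulative incidence with death without intubation as a competing event. This matches the NIV-group reporting in Statistical analysis.
2. If a two-arm outcome is wanted, use the proportion alive and free of invasive ventilation at day 30, with deaths counted as failures. It is defined in the same way in both arms.
3. Fit the logistic model for intubation in the NIV arm only, and do not force in ventilatory approach there.

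The cost is endpoint wording and a few lines of code. Data collection and follow-up already records ventilation settings daily until day 30 or the primary endpoint, and vital status at day 30 is collected. The small loss is the nominal two-arm intubation comparison. Counts of IMV patients actually intubated can still be reported as a description of adherence.

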### Study procedures

#### Recruitment

All 17 recruiting centers have substantial experience in treating immunocompromised patients with ARF. The 17 centers each admit 50 to 150 immunocompromised patients per year, 10 to 20% of whom meet VENIM inclusion criteria. Each center will screen subjects until the target population is achieved.

#### Randomization and blinding

Consecutive eligible patients will be randomly allocated in a 1:1 ratio to one of NIV or IMV. This study will include a total of 236 patients. Center 1 to Center 9 will each include 12 patients and Center 10 to Center 17 will each include 16 patients. Because the greatest common divisor of 12 and 16 is 4, we chose the block size 4. For this study, the statistician will produce computer-generated block randomization lists with SAS 9.4 (TS level 1 M2; Cary, NC, USA) stratified on the center. The randomization in blocks will be performed using opaque envelopes containing the IDs of the treatment group (NIV and IMV group). Then we will seal, shuffle the envelopes and number them in sequential order. For each eligible new patient, an envelope will be opened and then disclose the group allocation for this patient. The randomization day will be recorded as the study day zero (T0). We apply the PROBE Design [35] because ventilation cannot be blinded, and an effective sham measure is not available. Blinding to allocation of groups will be applied to the analysis.

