#### Exclusion criteria

Patients will be excluded from the study when:Age < 18 or >80 years old;Partial pressure of arterial carbon dioxide (PaCO_2_) > 50 mmHg [32] or arterial pH < 7.20;PaO_2_/FiO_2_ > 170 mmHg or PaO_2_/FiO_2_ < 85 mmHg;Patients have been treated with NIV, IMV or high-flow oxygen therapy within 30 days.NIV is contraindicated or IMV is definitely indicated, including PaO_2_/FiO_2_ < 85 mmHg, respiratory arrest, hemodynamic instability, inability to fit the face mask, pneumothorax, vomiting, development of airway bleeding, inability to protect the airway, or copious respiratory secretions;Comorbidity with acute-on-chronic ARF;Comorbidity with acute cardiac failure;HIV positive patients;Comorbidity with other severe diseases, including dilated cardiomyopathy, valvular heart disease, cardiogenic pulmonary edema, implanted cardiac pacemaker, or acute coronary syndrome; systolic arterial pressure < 90 mmHg after optimal fluid therapy; history of chronic obstructive pulmonary disease (COPD) or asthma; impaired consciousness (Glasgow Coma Scale score < 8), [33]; postoperative acute respiratory failure; pregnancy or breastfeeding; Lack of consent, do-not-intubate decision, and any other situations where obvious bias are expected.

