#### Coordination and conduct of the trial

Ahead of patient recruitment, all physicians and other health-care workers in the seventeen participating hospitals will attend formal training courses on the study protocol and data collection. Data will be recorded in electronic case report form (eCRF), which is a web response system available at each study center. eCRF system is provided and managed by the Emergency Department of Peking Union Medical College Hospital. All documents required for the study are available in each center. In each participating hospital, a medical team leading by at least one senior physician will be in charge of daily patient screening and inclusion, making sure compliance with the study protocol. The principal investigators will meet with the medical teams to evaluate study progress and to discuss any problems with protocol compliance and data collection.

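### Envelopes filled from a centre-stratified block list are shuffled before numbering, so the list is not the allocation order; if the blocks survive, a fixed block of 4 makes up to a third of allocations foreseeable

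*Protocol article*

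**What the plan says.** All of this stands in the protocol article, Randomization and blinding.

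- Allocation is 1:1: "Consecutive eligible patients will be randomly allocated in a 1:1 ratio to one of NIV or IMV".
- Size and quotas: "This study will include a total of 236 patients", and "Center 1 to Center 9 will each include 12 patients and Center 10 to Center 17 will each include 16 patients".
- Block size: "Because the greatest common divisor of 12 and 16 is 4, we chose the block size 4".
- Source of the sequence: "the statistician will produce computer-generated block randomization lists with SAS 9.4", with centre as the stratification factor.
- Concealment: opaque envelopes hold the group assignment. The next step is: "Then we will seal, shuffle the envelopes and number them in sequential order". One envelope is opened for each new eligible patient.

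The same section states that ventilation cannot be blinded and that only the analysis is blinded. The Design section calls the trial open-label. No varying block size and no central allocation is described.

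**The concern.** A stratified block list works only if patients are allocated in list order. Here the envelopes receive their numbers after they have been mixed, so the numbers follow the mixed order. The text promises stratified blocking and then describes a step that, taken literally, replaces the order on which the blocking depends.

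Leaving the shuffle out, or confining it to each block, exposes a different weakness. One fixed block size is published, each centre has its own short sequence of 12 or 16 patients, and every past allocation is visible to the team that screens the next patient. Staff who keep count can know some allocations before they decide on enrolment. If that knowledge influences who is enrolled, the arms differ at entry. Neither an objective endpoint such as 30-day mortality nor an intention-to-treat analysis corrects such a difference.

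**Working it through.** **Inputs** (Randomization and blinding): 1:1 allocation; 9 centres of 12 and 8 centres of 16; block size 4; one list per centre.

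**1. The plan's own figures.** 9 × 12 + 8 × 16 = 108 + 128 = 236, as stated. The greatest common divisor of 12 and 16 is 4, as stated. Blocks: 9 × 3 + 8 × 4 = 59, and 59 × 4 = 236. The quotas and the block size agree with each other. The article gives no figure for predictability, so steps 2 to 4 have nothing in the plan to match.

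**2. Blocks kept (no shuffle, or a shuffle inside each centre's block of 4).** A block has C(4,2) = 6 equally likely orders.
- AABB and BBAA: once one arm is used up, positions 3 and 4 are forced (2 each).
- ABAB, ABBA, BAAB and BABA: only position 4 is forced (1 each).
- Forced per block: (2 × 2 + 4 × 1)/6 = 8/6 = 1.333. Share: 1.333/4 = 33.3%. Over the trial: 59 × 1.333 = 78.7, about 79 of 236.
- Best guess by position: 1/2, 2/3, 2/3, 1. Mean: (1/2 + 2/3 + 2/3 + 1)/4 = 70.8%, against 50% with no information.

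**3. Shuffle across blocks within a centre.** The probability that every run of four is still 2:2 is 6^b / C(n, n/2), with b blocks and n patients.
- n = 12, b = 3: 216/924 = 23.4%.
- n = 16, b = 4: 1296/12870 = 10.1%.
- The centre total stays 1:1. With m patients per arm, the expected number of forced allocations is 2m/(m + 1): 12/7 = 1.714 for n = 12 and 16/9 = 1.778 for n = 16. Total: 9 × 1.714 + 8 × 1.778 = 29.7, or 12.6% of 236.

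**4. Shuffle pooled over all centres.** The probability of exact balance in a centre of n is C(n, n/2) × C(236 − n, 118 − n/2) / C(236, 118).
- n = 12: 23.2%. n = 16: 20.3%.
- A difference of 4 or more between arms: 37.5% (n = 12) and 43.8% (n = 16).
- A centre's own record never forces its next allocation, since at most 16 envelopes cannot use up an arm of 118.

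| Scope of shuffle | Blocks of 4 | Exact 1:1 in a centre | Certain in advance |
|---|---|---|---|
| None, or within each block | kept | yes | 33.3% (about 79) |
| Within a centre | survive with probability 23.4% or 10.1% | yes | 12.6% (about 30) |
| Across centres | lost | probability 23.2% or 20.3% | none from a centre's own record |

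Predictability is highest where the blocking is intact. The two weaknesses are alternatives and should not be added together.

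**The case against.** The strongest reply is that the scope of the shuffle is simply not stated. The sentence follows directly on a description of blocked randomization by centre, so it could mean mixing the four envelopes of one block. Blocks and strata would then survive. This stands: a reader might infer that the shuffle certainly destroys the stratified blocking, and the text does not support that much. It does support that the scope is undefined and that, even on the kindest reading, the order within a block comes from a manual shuffle and not from the SAS list.

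A fair shuffle also keeps allocation random. It costs balance and creates no bias, and this stands too.

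The article does describe safeguards: sealed opaque envelopes, consecutive enrolment, and consent and eligibility listed ahead of randomization in the participant timeline. They limit opportunity. They do not stop staff from working out the next allocation from earlier ones in a fixed block. Blinded analysis acts after entry.

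A block size that divides both quotas gives exact balance in every centre that fills its quota, so the stated reason for choosing 4 is not an error. It is only not a requirement.

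Three further inferences are tempting and do not hold:
- **That the sequence cannot be audited.** The article does not say whether the numbered order is logged, and envelope handling is commonly left to the full protocol.
- **That the exclusion of "any other situations where obvious bias are expected" is the route by which staff would act on a foreseen allocation.** The wording is loose, but that use is conjecture, and removing it would repair neither randomization problem.
- **That the eCRF can already randomize.** It is described as "which is a web response system available at each study center", for recording data only.

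**Conclusion.** The point holds in two conditional parts.

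First, as written, the allocation order is not the generated list. Unless the shuffle is confined to each centre's block of 4, which the article does not say, the stated blocking is lost. Centre balance is lost as well if envelopes are pooled across centres. The damage is to balance.

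Second, if the blocks are kept, up to 33.3% of allocations are certain in advance and best guessing succeeds 70.8% of the time. This assumes that staff know the block size, track every earlier allocation at their centre and work from one sequence per centre. It is therefore an upper bound on certain knowledge and not a forecast of misuse.

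A reader might infer that 30-day mortality is already biased. Nothing in the article shows that selection occurred, and the size of any bias cannot be computed from it. What is shown is an avoidable exposure of the primary comparison, together with a procedure that cannot be followed consistently as described.

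**What to change.** 1. Delete the shuffle. Have the coordinating centre number the envelopes in list order, separately for each centre.
2. For remaining patients, generate new centre-stratified lists with randomly varying block sizes (for example 2, 4 and 6), and do not disclose the sizes to sites.
3. Enrolment began in January 2017 (Trial status), so record how the envelopes already issued were ordered and numbered.
4. Optionally, allocate centrally over the web once eligibility is confirmed, if the existing eCRF proves able to support it.

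Cost: a new list for remaining patients, and a possible imbalance where a centre stops inside a block. With blocks of at most 6 this is at most 3 patients per centre. Such differences can add up over 17 centres. Varying undisclosed blocks reduce predictability but do not abolish it.
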